### Interventions and Comparators

#### Intervention

The simulator will be first administered at the March training weekends for each year. We will use these training weekends to test participants at baseline on the simulator and collect demographic data via survey. The simulator will be set up as one of the 15-minute assessment stations in the training weekend. Simulator sets will be distributed to individual trainees following the training weekend. Upon delivery of the simulator sets, the principal investigator will also provide aid to the trainee in identifying an appropriate environment for the simulator and address any setup issues.

It is then expected that trainees will undertake, at minimum, monthly 15-minute practices on the simulator for the next 6 months of training. These practice data are sent to a cloud server after each use. Note that the simulator training will be in addition to any routine training they will receive at their respective hospitals. Over this time, primary end points for each in-theater case will be taken over the course of follow-up through District Health Board (DHB) records, including patient picture archiving and communication system (PACS) records and trainees’ logbooks.

We will request intervention trainees to write out relevant patient data and end point results as the cases present to maximize accuracy. Trainees will be reminded monthly by email to provide case data and practice on the simulator. Their simulator performance will be assessed again in a controlled environment during the November training weekend. At this point, secondary end points will also be collected via survey.

#### Comparators

The comparator cohort’s follow-up will begin in February of each year. This is due to the change to the training schedule instated at the end of 2020 whereby trainees began their rotations in February instead of the prior December.

Primary outcomes will be collected retrospectively via trainee logbooks and patient PACS records for retrospective data. Secondary outcomes will not be collected for comparators.

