**Methods:**

This multicenter, interventional cohort study will involve orthopedic trainees from New Zealand in their first year of advanced training between 2019 and 2023. Advanced trainees with no simulator exposure who were in their first year in 2019-2021 will form the comparator cohort, while those in the years 2022-2023 will receive additional regular simulator training as the intervention cohort. The comparator cohort’s performance in pediatric SCHF surgery will be retrospectively audited using routinely collected operative outcomes and parameters over a 6-month period. Data on the performance of the intervention cohorts will be collected in the same way over a comparable period. The data collected for both groups will be used to determine whether additional training with an augmented reality training shows improved real-world surgical outcomes compared to traditional surgical training.

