### Study Design

The intervention cohort is composed of trainees using the BoneDoc AR simulator at least once per month over a follow-up period of 6 months (May to November) in the years 2022-2023 (Figure 1).

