### Recruitment

Intervention group trainees will be approached at training weekends to inform them about the study, to assess eligibility, and to receive consent. Comparator group trainees will be identified from the New Zealand Orthopaedic Association trainee registry and approached via email for this process. Enrollment for comparator group trainees will begin in February 2022, and enrollment for intervention group trainees will occur in the March training weekends of 2022 and 2023.

We aim to include data for 14 trainees in 2022; however, the number of trainees in 2023 is not yet known. The comparator cohort data will be retrospectively audited from trainees who undertook traditional training without exposure to the simulator during their 6 months of follow-up in the years 2019, 2020, and 2021 (n=41). We expect a total sample size of approximately 65 trainees, given an average of 12 new trainees per annum. The comparator group is matched based on their length of registered training at the start of follow-up, that is, first-year trainees with 2 months of registered training.

The in-theater performances of the comparator and intervention groups will be compared using cumulative sum charts for each of the primary outcomes to determine any differences in trends of skill acquisition according to the method of training. The simulator performance of the intervention group will be used to establish a learning curve and compared with in-theater learning curves.

Retrospectively matched trainees have been chosen instead of prospective randomized ones for the comparison group in order to maximize sample size and to avoid contamination. New Zealand only introduces 10-15 trainees per year into the orthopedic training program, and thus a prospective randomized trial will greatly limit the statistical power. There is also the chance of cross-group contamination as there is no way of ensuring comparator trainees located in the same area as intervention trainees will not use the simulator.

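### The cohorts are said to be matched at 2 months of training, but the stated calendars give about 2 months (2019-2020), 0 (2021) and 3 (intervention, or 1 to 2 if counted from the March weekend)

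*Protocol article*

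**What the plan says.** Five places in the protocol article bear on when each trainee's observation starts.

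- **Recruitment** gives the matching rule: comparators are "first-year trainees with 2 months of registered training" when follow-up starts. The comparators are audited "during their 6 months of follow-up in the years 2019, 2020, and 2021 (n=41").
- **Comparators** says their "follow-up will begin in February of each year" and explains this by the "change to the training schedule instated at the end of 2020 whereby trainees began their rotations in February instead of the prior December".
- **Study Design** has the intervention cohort using the simulator "over a follow-up period of 6 months (May to November) in the years 2022-2023".
- **Intervention** has first simulator use at the March training weekend, then "monthly 15-minute practices on the simulator for the next 6 months of training", with in-theater end points gathered over that time.
- **Abstract, Methods** says the intervention data will be "collected in the same way over a comparable period".

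Strengths and Limitations names matching on training experience as a means of limiting confounding from the historical comparator. Outcomes says that theater time and radiation exposure have been shown to fall as trainees become more proficient.

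**The concern.** The comparison is not randomised, and training time at the start of follow-up is the only variable on which the cohorts are said to be matched. The outcomes are learning-curve outcomes, plotted as cumulative sum charts to compare trends in skill acquisition. Such a comparison needs a common starting point. If one cohort is observed later in training than the other, part of any difference in theater time or fluoroscopy shots reflects training stage and not the simulator.

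The reason given for the February start makes the problem visible. February yields 2 months of prior training only for trainees who began the previous December. The same February start is nevertheless applied to every comparator year, including 2021, after rotations had moved to February.

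**Working it through.** **Inputs.** Rotation starts and comparator follow-up start: Comparators. Intervention follow-up: Study Design (May), or Intervention (after the March weekend). Matching criterion, comparator n=41 and annual intake of 10-15: Recruitment.

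**Assumptions.** Rotation start is the start of registered training. The 2021 intake began in February 2021, as the wording in Comparators indicates. The February start continued in 2022-2023.

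**Step 1. Months of training at the start of follow-up** = follow-up start month minus rotation start month. The window adds 6 months.

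| Intake | Rotation start | Follow-up start | Months at start | Training months observed |
|---|---|---|---|---|
| 2019, 2020 comparators | December before | February | 2 | 2 to 8 |
| 2021 comparators | February | February | 0 | 0 to 6 |
| 2022, 2023 intervention (Study Design) | February | May | 3 | 3 to 9 |
| 2022, 2023 intervention (Intervention, from March) | February | March | 1 | 1 to 7 |
| 2022, 2023 intervention (Intervention, from April) | February | April | 2 | 2 to 8 |

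The stated 2 months is reproduced for 2019 and 2020 only. The intervention cohort reaches it only with an April start, which no section states.

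**Step 2. Gap by year under the May start.** 3 − 2 = 1 month against 2019-2020, and 3 − 0 = 3 months against 2021. The 2021 comparators (months 0 to 6) share only months 3 to 6 of training with the intervention cohort (months 3 to 9), half of the window.

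**Step 3. Mean gap.** The split of the 41 comparators by year is not given. With n₂₁ of them from 2021, the comparator mean is 2 × (41 − n₂₁)/41.

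- n₂₁ = 10: 2 × 31/41 = 1.51 months.
- n₂₁ = 15: 2 × 26/41 = 1.27 months.

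| Intervention start | Gap, n₂₁ = 10 | Gap, n₂₁ = 15 |
|---|---|---|
| May (3 months) | 3 − 1.51 = +1.49 | 3 − 1.27 = +1.73 |
| April (2 months) | 2 − 1.51 = +0.49 | 2 − 1.27 = +0.73 |
| March (1 month) | 1 − 1.51 = −0.51 | 1 − 1.27 = −0.27 |

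These means suppose that all 41 take part. Only 8 had been recruited by February 2022, so the realised mix of years may differ.

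**Step 4. Rounding.** No section gives days. From late February to 1 May is about 2 months, so the 1-month gap to 2019-2020 lies within the precision of month names. The 2021 result does not: a rotation starting on 1 February and follow-up starting at the end of February still gives less than 1 month, against a criterion of 2.

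**The case against.** A reader might infer that a bias of known size in favour of the simulator is built into the cohort definitions. The document does not support that, for four reasons.

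- **Direction.** It depends on the May start. The Intervention section can be read as collecting end points from the March weekend, and then the mean gap is near zero or slightly reversed.
- **Missing figure.** Figure 1 is the timeline for both cohorts and cannot be seen here. It may settle which intervention window is meant.
- **Size.** Outcomes says the measures fall with proficiency but gives no rate. Multiplying the gap by a monthly improvement would be guesswork, and the trainees are not novices.
- **Existing safeguards.** Statistical Analysis lists SCHF procedures performed before and during the intervention as independent variables. Strengths and Limitations plans to explore baseline confounders and to run a difference-in-difference analysis. Prior case count is arguably closer to the learning curve than calendar months.

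The first three points stand, and they limit the claim to inconsistent windows with a conditional direction. The fourth stands only in part. The main group comparisons are unadjusted t, Wilcoxon, chi-square or Fisher tests. Months of training is not a listed covariate. Prior procedures enter a multivariable model only if univariable P<.05, a screen that can drop a real confounder in a sample of about 65 trainees. A difference-in-difference analysis of learning curves is itself affected when the curves start at different stages of training. None of the four points brings the 2021 comparators to 2 months.

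**Conclusion.** The matching rule and the stated calendars contradict each other, and the sections must be reconciled before the records are pulled and analysed. The firm part is the 2021 intake: about 0 months against a criterion of 2, whichever intervention start is meant. This rests on rotation start being the start of registered training and on a February 2021 start. Had that intake begun in December, it would have had 2 months.

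Under the explicit May to November window, which also assumes that the February start continued, the intervention cohort is observed about 3 months later in training than the 2021 comparators and about 1 month later than the 2019-2020 comparators. The mean difference is about 1.5 to 1.7 months if 10 to 15 of the 41 are from 2021. On the protocol's own account of proficiency, that would favour the simulator. Under a March start it would not. How much of any observed difference would be due to this cannot be worked out from the document.

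**What to change.** Define follow-up in months since each trainee's own rotation start, apply one common 6-month window to all intakes, and make Study Design, Recruitment, Intervention, Comparators and Figure 1 agree. Two versions work.

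1. **Keep the May start.** Use May to November for February starters (2021-2023) and March to September for December starters (2019-2020). Restate the criterion as 3 months.
2. **Keep the 2-month criterion.** Start follow-up in February for December starters and in April for February starters, giving February to August and April to October.

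The first leaves the stated intervention window untouched. Both give the 2021 comparators the same training stage and season as the intervention cohort.

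In either case, include time since rotation start, or the trainee's running SCHF case number, in the group comparison regardless of the P<.05 screen. A sensitivity comparison against the 2021 comparators alone is optional and would be small.

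The cost is a wording change and a different date range in the logbook and record pull. No new participants are needed. A seasonal difference of about 2 months remains for the 2019-2020 comparators (March against May, or February against April).

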### Data Collection

#### Outcomes

##### Primary End Points—Collected for Each In-Theater Case Over Follow-up

Theater time and radiation time in seconds (radiation time may not be available from retrospectively assessed notes but will be attained where possible)—collected from procedure reports from electronic patient recordsNumber of fluoroscopy shots—collected from patient PACS recordsPin accuracy—accuracy is defined based on procedural recommendation literature—analyzed from patient PACS recordsComplication/nonideal union incidence—stratified for types of complications (nerve injury, vascular injury, loss of reduction, compartment syndrome, and infection)—collected from reviews of medical records and letters of referral from electronic patient notes

These primary end points have been determined as measurements of trainee performance, which are relatively easily retrieved from patient records and trainee logbooks.

The number of fluoroscopy shots and radiation time can be used to approximate the amount of radiation patients and staff are exposed to. In particular, for patients, theater time and radiation exposure have been shown to correlate to a higher chance of complications and thus should be avoided [21]. Studies have shown a decrease in both measurements for SCHF treatments with increased trainee proficiency [22,23]. Pin accuracy affects the stability of union, and there are well-established guidelines for ideal position of pins.

Ultimately, postoperative complications and nonideal union are the most crucial outcomes the trainees should aim to avoid. We do not expect to see high rates of these for either group, but overall rates will be monitored for comparison.

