**Conclusions:**

This protocol has been approved by the University of Otago Health Ethics committee (reference HD21/087), and the study is due for completion in 2024. This protocol may assist other researchers conducting similar studies in the field.

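### Complications and nonideal union are tied to the trainee's 6-month follow-up and not to a fixed time since surgery, so ascertainment may differ between cohorts or fall with case order

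*Protocol article*

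**What the plan says.** The Outcomes section heads the list "Primary End Points—Collected for Each In-Theater Case Over Follow-up". Complications and nonideal union are on it, with their source given as "collected from reviews of medical records and letters of referral from electronic patient notes". Follow-up is defined for the trainee: 6 months, May to November of 2022 and 2023, for the intervention cohort (Study Design), and 6 months starting in February of 2019 to 2021 for the comparators (Recruitment; Comparators).

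On how the data are gathered, the article says:

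- Intervention: "primary end points for each in-theater case will be taken over the course of follow-up through District Health Board (DHB) records", and "We will request intervention trainees to write out relevant patient data and end point results as the cases present to maximize accuracy".
- Comparators: "Primary outcomes will be collected retrospectively via trainee logbooks and patient PACS records for retrospective data". Their enrolment starts in February 2022 (Recruitment).
- Both, in the abstract: "Data on the performance of the intervention cohorts will be collected in the same way over a comparable period".
- Timing of the end: "the study is due for completion in 2024", with no month given.

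The Statistical Analysis section compares numbers of complications by chi-square or Fisher exact test and models them by ordinary least squares. It also plots each primary end point on cumulative sum curves to show trends over follow-up. Time under observation is not among the listed independent variables.

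**The concern.** Theater time and fluoroscopy shots are complete when the operation ends, so a trainee-level period suits them. Complications and nonideal union arise, or are written down, afterwards. For them the trainee's 6 months says which operations count, but not how long each patient is observed. A case in the first week can be watched for about 6 months and one in the last week for days, unless the record search runs on past follow-up, and the article does not say whether it does.

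Two things are at stake. First, if the search length differs between cohorts, equal surgical results can give unequal counts, and the planned tests have no means of correcting this. Second, if observation shortens as follow-up proceeds, a constant complication rate appears to fall with case order, which is the pattern a learning curve is meant to detect. The protocol describes these outcomes as the ones trainees should most aim to avoid, while expecting them to be infrequent.

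**Working it through.** The plan gives no figure for observation time, so there is none to reproduce on this point. Its only sample-size figure is the head count, 41 + 2 × 12 = 65, which is unaffected.

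**Step 1. Record time available per case if the search is open-ended.** Inputs from the document: comparator follow-up from February for 6 months, comparator enrolment from February 2022, intervention cases May to November. Calendar bounds used here: 1 February to 31 July for comparators, 1 May to 30 November for intervention.

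| Cases | Search date | Months of records |
|---|---|---|
| Comparator 2019 | 1 Feb 2022 | 30–36 |
| Comparator 2020 | 1 Feb 2022 | 18–24 |
| Comparator 2021 | 1 Feb 2022 | 6–12 |
| Intervention 2022 | end Nov 2023 | 12–19 |
| Intervention 2023 | end Nov 2023 | 0–7 |
| Intervention 2023 | end Jan 2024 | 2–9 |
| Intervention 2023 | end June 2024 | 7–14 |
| Intervention 2023 | end Dec 2024 | 13–20 |

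**Step 2. Effect on the cohort comparison.** Assumptions, none from the document: true risk 10% in both cohorts; delay from surgery to a recorded event exponential with mean m months; cases spread evenly over follow-up; calendar years weighted equally. For cases whose windows run evenly from a to b months, the share of events recorded is

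1 − m(e^(−a/m) − e^(−b/m)) / (b − a).

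Example with m = 3. Intervention stopped at the trainee's 6 months (a = 0, b = 6): 1 − 3(1 − e^(−2))/6 = 0.568, so an apparent rate of 5.7%. Comparators at February 2022: 10.0%, 10.0% and 9.4% for 2019, 2020 and 2021, mean 9.8%. Ratio 5.68/9.80 = 0.58.

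Apparent rate in %, with the ratio to the open comparator search in brackets:

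| m | Comparator, open, Feb 2022 | Intervention stopped at 6 months | Open, lock end Nov 2023 | Open, lock end Jan 2024 | Open, lock end June 2024 | Open, lock end Dec 2024 |
|---|---|---|---|---|---|---|
| 0.5 | 10.0 | 9.2 (0.92) | 9.6 (0.96) | 10.0 (1.00) | 10.0 (1.00) | 10.0 (1.00) |
| 1 | 10.0 | 8.3 (0.83) | 9.3 (0.93) | 9.9 (0.99) | 10.0 (1.00) | 10.0 (1.00) |
| 3 | 9.8 | 5.7 (0.58) | 8.0 (0.82) | 9.0 (0.92) | 9.8 (1.00) | 10.0 (1.02) |
| 6 | 9.1 | 3.7 (0.40) | 6.7 (0.73) | 7.6 (0.84) | 9.0 (0.98) | 9.6 (1.06) |

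If the comparator audit ran instead on 1 December 2023 (windows of 28 to 58 months), its apparent rate would be 10.0% for every m shown, and the ratio at an end-June 2024 lock would be 0.98 for m = 3 and 0.90 for m = 6.

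**Step 3. The 6-month cut-off applied to both cohorts.** Both then show the same apparent rate (9.2% down to 3.7% as m goes from 0.5 to 6), so the crude ratio is 1.00. Within follow-up, first-month cases have 5 to 6 months of observation and last-month cases 0 to 1:

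- m = 1: 10.0% in the first month, 3.7% in the last.
- m = 3: 8.4% in the first month, 1.5% in the last.

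The true risk is constant throughout, so the whole fall is an artefact.

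**The case against.** A condensed article often leaves ascertainment windows to the full protocol or analysis plan, and a missing window alone would be no finding. What takes this further is that the article does attach a period to the end point, and that period does not fit an outcome arising after surgery.

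A reader might infer that the plan favours the simulator, with years of comparator records set against weeks for late intervention cases. The document does not support that.

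- The abstract promises collection in the same manner over a comparable period. Read that way, both cohorts are cut off alike and the crude comparison is unbiased.
- Only intervention trainees are asked to write results down case by case, with monthly email reminders. The Comparators section names logbooks and PACS for that cohort, and neither medical records nor letters. Both differences could raise detection in the intervention cohort.
- Years of records holds for 2019 and 2020 cases, but 2021 cases have only 6 to 12 months at a February 2022 audit. The short window affects only late cases if both searches are open, and then only the 2023 intake with an early lock. Completion in 2024 may allow 13 months or more even for the last case.

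These points stand, and they remove any claim of a known direction. They do not remove the defect: the article does not say which reading applies, and no listed analysis allows for observation time. The difference-in-difference analysis mentioned in the Discussion would cancel a truncation shared by both cohorts, but not one confined to the intervention cohort.

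**Conclusion.** The concern holds in a limited form. A primary end point is tied to the trainee's follow-up rather than to time since surgery, and the consequence depends on a reading that the article leaves open.

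- **Open comparator search, intervention stopped at follow-up:** false ratio of 0.92 to 0.40 for m from 0.5 to 6 months, with the fall over case order confined to the intervention cohort.
- **Open search in both cohorts:** 0.96 to 0.73 with a lock at end November 2023. The difference is small from mid-2024 (0.98 to 1.00 against a February 2022 comparator audit), except where recording is slow and comparators are also audited late (0.90).
- **Cut-off in both cohorts:** no bias in the crude comparison, but under-counting and a false downward trend in the complication cumulative sum chart.

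The sizes rest on the assumed 10% risk and exponential delay. They are slight for events noted soon after surgery and larger for those recorded late, as nonideal union may be. They isolate observation time and leave out the source and recording differences, so they are not an estimate of net bias. Longer comparator observation alone would favour the simulator; the net direction is not settled. This should be corrected, but it does not invalidate the study.

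**What to change.** Define the end point by one interval counted from the date of surgery, identical for both cohorts, and count a complication or nonideal union only if it is recorded within it. State further that:

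- the interval is not truncated at the end of the trainee's 6 months;
- both cohorts are ascertained from the same sources, the medical records and referral letters already named under Primary End Points, since a date rule alone would leave the source difference in place;
- the interval is one that every case can complete, and data are locked only after the last November 2023 case has completed it;
- later events are reported descriptively.

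Under the assumptions above, with sources and recording alike, expected detection is then equal at equal true risk (ratio 1.00) and does not depend on case order. The expected 65 trainees are unchanged. The cost is protocol wording, a date filter, and record and letter review for comparators where only logbooks and PACS were intended. Late comparator events leave the main count, and 2023 records are pulled somewhat later.
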